#### Retention plan

To maximize retention, assessments are conducted individually. This reduces the burden of coordinating scheduling with relationship partners and permits the retention of participants even if relationships dissolve during the follow-up period. In addition, study staff remain in regular (at least quarterly) contact with participants through email, text messaging, and telephone (based on participant preference). This provides the opportunity to regularly update contact information and maintain consistent engagement throughout the follow-up period.

#### Data management

All survey instruments are administered using a Qualtrics-based computer-assisted survey instrument (CASI) interface. To reduce the time required to attend the remote baseline appointment, participants have the option of completing the baseline survey before the appointment . TLFB data are gathered by a trained interviewer using a data-entry system programmed in Microsoft Access (see below for additional details). The following sections also provide specific details related to the handling of biological specimens and related results. Study procedures have been reviewed by  the CUNY University Integrated Institutional Review Board (CUNY-UI IRB). In addition, we have set up a Data Safety Monitoring Board consisting of leading experts in sexual minority men with particular specific expertise in randomized controlled trials, epidemiology, statistical analysis, and clinical research broadly.

### Data analysis plan

#### Data screening procedures and analyses of attrition

We will follow standard procedures in cleaning data and examining distributional properties (means, standard deviations, skew, kurtosis, and visual representations). Subsequently, we will conduct an analysis of attrition to determine if dropout is associated with 1) demographic variables and/or 2) drug use or TRB outcomes assessed at baseline. Factors which are observed to covary significantly with attrition will be incorporated in outcome analyses. [name] (Co-I) is an accomplished epidemiologist who is familiar with modeling procedures applicable to the modeling of variables with non-normal distributions (i.e., categorical and count variables), and we will utilize appropriate tests of association and linking functions in statistical models. [name] will utilize Mplus (version 8.0) [12] in conducting these analyses.

Analyses will utilize a true intent-to-treat procedure involving data from all randomized couples. Mplus has a variety of options for handling partial attrition including full-information maximum likelihood estimation. Non-random and consequential missingness can also be modeled directly through the addition of latent variables which account for the probability of missingness at any time point.

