#### Sample size

Power analyses were generated by Monte Carlo simulation using Mplus (version 8.0). All estimates were based upon 10,000 sample replications and power was defined as the percentage of randomly generated samples in which the specified parameter was statistically significant. All simulated models were multi-level, nesting participants (at Level 1) within couples (at Level 2). Models focused on detecting between-condition differences at any one follow-up time-point (as opposed to predicting slope factors). This allowed for more direct extrapolation of error variances from existing baseline data and is consistent with the primary aim of the study. The main effects of the two interventions (the drug use calendar and video-based communication skills training) as well as their interaction were modeled at level 2. Based upon the results of our previous studies, we anticipate 80% minimum follow-up retention at 12 months. These analyses therefore reflect a conservative analytic sample of 240 couples (480 individuals).

Analyses indicated that the proposed study has power > .80 to detect a simple main effect of SUM and/or CT videos corresponding to a 15% reduction in the odds of drug use and a 1.0 point reduction in DAST scores at any follow-up time point. The proposed study has power > .80 to detect a 2% reduction in the odds of reporting HIV TRB. Effects of these magnitudes are plausible given our pilot data. *We Test* pilot data have indicated that mediational pathways linking CT videos with drug use outcomes likely involve depression. The effects of viewing ACTV were generally small across indices of communication skills and psychological functioning. The most promising (statistically significant) effects were associated with improvements in self- disclosure communication (β = .13) and depression (β = −.16). Notably, the indirect pathway between CT and depression through self-disclosure communication was of moderate size (β = −.12) indicating that communication skills may be one mechanism by which ACTV yields reductions in depression. Depression scores were, in turn, positively associated with the odds of drug use (β = −.45) and DAST scores (β = .06). Using these effects as preliminary estimates, Monte Carlo simulations suggested that the proposed study design has power > .80 to detect the significance of direct pathways and implied indirect effects of intervention.

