### Methods: assignment of interventions

#### Randomization

Couples will be randomly assigned to 1 of 4 conditions, CHTC as usual, CHTC + SUM, CHTC + CT video, or CHTC + SUM + CT video using a stratified block randomization procedure programmed in Qualtrics. Specifically, randomization will account for baseline report of: (1) relationship length (4 years or less/greater than 4 years) and (2) race/ethnicity makeup of the couple, for example, both partners identify as white and non-Hispanic/one or both partners identify as non-white or Hispanic. The random assignment will be performed by the assigned study interventionist immediately prior to intervention delivery.

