#### Primary analyses of intervention effects

Outcome variables will be tested by applying a multilevel latent growth model to follow-up data, accounting for nesting within couples. Models will utilize 5 data points (Baseline, 3-, 6-, 9-, and 12-month follow up) and full-information maximum likelihood estimation to ensure that all randomized participants are included in analyses – consistent with the ITT paradigm. Models will include an intercept (representing the initial outcome value) and two slope factors. The first slope-coefficient will quantify change from baseline to post-intervention. The second will capture change over time post intervention. Mplus accommodates count and dichotomous outcomes. Growth factors will then be regressed on intervention condition at the couple level (Level II) and the effect of the intervention will be evaluated by examining the regression coefficient (and associated *p* value) associated with intervention condition for each of these factors.

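### Covariates enter the outcome models through a significance test on observed dropout, so the primary model is not fixed until follow-up data are seen

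*Protocol article*

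**What the plan says.** Only the protocol article is at hand. Under 'Data screening procedures and analyses of attrition' it plans an attrition analysis to "determine if dropout is associated with 1) demographic variables and/or 2) drug use or TRB outcomes assessed at baseline". It then gives the rule: "Factors which are observed to covary significantly with attrition will be incorporated in outcome analyses". The significance threshold, the number of candidate factors and the visit that defines dropout are not given.

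Under 'Primary analyses of intervention effects' the model is a multilevel latent growth model on five data points, baseline included. There, "Growth factors will then be regressed on intervention condition at the couple level (Level II"). No other predictor is named. Estimation is by "full-information maximum likelihood estimation to ensure that all randomized participants are included in analyses".

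Under 'Randomization', allocation is stratified on "1) relationship length (4 years or less/greater than 4 years) and (2) race/ethnicity makeup of the couple". Neither factor reappears in the description of the outcome model.

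On missingness that depends on unobserved values, the article says: "Non-random and consequential missingness can also be modeled directly through the addition of latent variables". This describes an option and does not commit to it.

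**The concern.** Full-information maximum likelihood (FIML) relies on the data being missing at random given what is in the model. The variables that help are those related to both the outcome and dropout, whether or not a dropout test reaches significance in one sample. The stated rule looks at dropout alone. It can leave out a real but modest predictor of dropout that is strongly prognostic, and it can bring in a factor that is linked to dropout by chance and has no bearing on the outcome.

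The rule also means that the covariate set of a confirmatory model is settled only once dropout has been observed. Race/ethnicity is both a demographic and, at couple level, a stratification factor. On the text as written, its place in the model could turn on a dropout p-value, although it was used in allocation and is known in advance. What is at stake is mainly pre-specification and efficient use of baseline information, rather than the validity of the randomised comparison.

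**Working it through.** The article gives no figure for this selection step, so there is none to reproduce. The inputs are as follows.

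- **Sample.** The article says "we anticipate 80% minimum follow-up retention at 12 months" and gives an analytic sample of 240 couples, that is 2 × 240 = 480 people. The number randomised is not stated. If 240 is what remains at 80%, then 240 / 0.80 = 300 couples, or 600 people (inferred).
- **Attrition.** 1 − 0.80 = 20%.
- **Test level.** Two-sided 0.05 (assumed).
- **Clustering.** Ignored first, then bounded.
- **Candidates.** 8 to 12 (assumed). For scale, the article names four demographic factors under moderation (race/ethnicity, age, income, education) and five outcome indicators (self-reported drug use, urine assay, three TRB indicators): 4 + 5 = 9.

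**1. Chance that a real predictor of dropout is selected.** For a logistic regression of dropout on a standardised factor:

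SE(log OR) ≈ 1/√(N·p·(1 − p)) = 1/√(600 × 0.2 × 0.8) = 1/√96 = 0.102

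P(selected) ≈ Φ(ln OR / SE − 1.96)

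- OR 1.2 per SD: 0.182/0.102 = 1.79, and Φ(1.79 − 1.96) = 43%. It is missed 57% of the time.
- OR 1.3 per SD: 0.262/0.102 = 2.57, and Φ(2.57 − 1.96) = 73%. It is missed 27% of the time.

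At the clustering extreme, partners share the factor and leave together, so the effective N is 300. Then SE = 1/√48 = 0.144, and the selection chances fall to Φ(1.26 − 1.96) = 24% and Φ(1.82 − 1.96) = 44%.

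For an evenly split binary factor, attrition of 15% versus 25% is flagged with probability 87% (600 units) or 58% (300 units). For 17.5% versus 22.5% the figures are 33% and 19%.

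**2. Chance that an unrelated factor enters.** With k independent null tests, P(at least one) = 1 − 0.95^k.

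- k = 8: 34%
- k = 9: 37%
- k = 12: 46%

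**3. Does the rule damage the test of the intervention?** A single-visit logistic simulation (600 people, one strongly prognostic covariate, complete cases, no clustering, 2,000 replicates, all parameters assumed) applied the rule under no intervention effect. Type I error was 4.8% when dropout was unrelated to the covariate, and 4.4% when dropout had the same relation to it in both arms. In these two settings the rule does not inflate false positives.

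**The case against.** The strongest reply is that the article does not say that no other covariates will enter. It is a condensed account, and a full covariate list is commonly left to an analysis plan that is not shown. That is fair: a reader might infer that the significance test is the only route into the model, but the text does not say so. What stands is narrower. The article does state and fix a selection rule, and an analysis plan that followed it would inherit the weakness.

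Three stronger readings are tempting, and the documents do not support them.

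- **The target of estimation shifts materially.** In the single-visit simulation with a true log odds ratio of −0.6, the average estimate under the rule was −0.44 when the covariate was rarely selected and −0.60 when it usually was. The planned model, however, has person-level latent growth factors that already absorb much of that heterogeneity. In a simplified repeated-measures version (five visits, random intercept, dropout related to the covariate equally in both arms, 100 replicates), the mean estimates were −0.578 without the covariate and −0.580 with it. The shift largely does not carry over.
- **Differential dropout by condition is a missing key check and would go unreported.** Nothing says that attrition by arm will not be reported. Condition is already in the model, so dropout depending on condition alone is ignorable under FIML, and its absence from a list of factors that might be added is natural.
- **Type I error is badly inflated.** The single-visit simulation gave 22.7% under the rule, against about 5% with the covariate fixed in advance. It did so only when dropout depended on a strong covariate in opposite directions by arm and was analysed as complete cases. In the repeated-measures version of crossed dropout the bias was −0.15 without the covariate and −0.05 with it. Nothing in the article suggests such a pattern.

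The outcome's own baseline value is already one of the five modelled data points, so the rule cannot remove it.

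**Conclusion.** The point holds as a minor one. The article selects covariates by a dropout significance test, while the described primary model names no fixed covariates and does not carry in the stratification factors. Under the assumptions stated (600 people, 20% attrition, a 0.05 threshold, independent individuals), the rule misses a predictor with OR 1.2 per SD 57% of the time. It admits at least one of 8 to 12 unrelated factors in 34% to 46% of trials. Allowing for clustering makes missing real predictors more likely.

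These figures measure how unstable the selection is. They do not measure harm to the conclusion. An irrelevant baseline covariate does little damage in a randomised comparison, and the bias from an omitted one is probably modest given FIML and the modelled baseline. The case for change is that the primary model should be known before follow-up data are seen.

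**What to change.** Replace the significance rule with a fixed set, used whatever the attrition tests show:

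- **Covariates:** the two stratification factors (relationship length and race/ethnicity makeup of the couple) and site.
- **Auxiliary variables in the FIML likelihood:** a pre-listed set of baseline demographic, drug use and TRB variables, with a sentence on how they enter given dichotomous outcomes. The outcome's own baseline need not be added.

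Keep the attrition analysis as description. As a minor addition, include assigned condition and condition by baseline drug use in it.

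The cost is a change of wording in the analysis plan, one extra descriptive table and a few more model parameters. No change to data collection or sample size is needed.

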#### Primary analyses of intervention effects

Outcome variables will be tested by applying a multilevel latent growth model to follow-up data, accounting for nesting within couples. Models will utilize 5 data points (Baseline, 3-, 6-, 9-, and 12-month follow up) and full-information maximum likelihood estimation to ensure that all randomized participants are included in analyses – consistent with the ITT paradigm. Models will include an intercept (representing the initial outcome value) and two slope factors. The first slope-coefficient will quantify change from baseline to post-intervention. The second will capture change over time post intervention. Mplus accommodates count and dichotomous outcomes. Growth factors will then be regressed on intervention condition at the couple level (Level II) and the effect of the intervention will be evaluated by examining the regression coefficient (and associated *p* value) associated with intervention condition for each of these factors.

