#### HIV transmission risk behavior (TRB)

Primary Analyses focus on three dichotomous behavioral indicators of TRB These include: (1) Condomless anal sex (CAS) with a casual partner in the absence of PrEP; (2) CAS with a sero-discordant main partner (whose viral load is detectible) or concurrent CAS between main and casual partners in the absence of PrEP; (3) Any chlamydia or gonorrhea diagnosis in the absence of PrEP.

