#### Moderation/mediation analyses

We will conduct analyses to identify putative moderators and mediators of intervention effects. Moderation analyses will focus on demographic factors that have been linked to HIV disparities. Specifically, we will examine whether the effect of the intervention is constant across race and ethnicity, age, and indicators of socioeconomic status (income and education) in all proposed analyses. We will also examine whether intervention effects vary across couples’ HIV status, incorporating attention to viral suppression and PrEP uptake.

We utilize the actor–partner interdependence model (APIM) Kenny et al. [6] to organize individual-level mediators. APIMs are multilevel models. At the individual level (Level 1), there are two types of effects: *actor* (the association between an individual’s score on an outcome and his own score on a predictor) and *partner* (the association between an individual’s score on an outcome and his partner’s score on a predictor). Couple-level (Level 2) effects are calculated for variables where both partners share a score (e.g., relationship length).

A series of APIMs will be calculated to examine putative mediators. Due to model complexity, each drug and TRB outcome will be examined separately. As with primary outcome analyses described above, we will utilize growth modeling procedures to calculate an intercept and slope for each outcome over time. Similarly, models will also specify growth factors for mediators at Level 1 and Level 2 during the follow-up period. In this manner, growth factors for the outcome can be regressed on growth factors for the putative mediator at both Level 1 and Level 2. Subsequently, the effect of intervention (a couple-level predictor) will be determined by examining the regression coefficients associated with intervention in the prediction of growth factors for both the outcome of interest and the mediator at Level 2. Where indicated by the pattern of significant direct effects, indirect pathways from intervention condition through actor and partner effects of the mediator will be tested using bootstrapping tests of mediation. Where outcome distributions prevent the use of bootstrapping, we will utilize a model constraint approach to evaluating the significance of indirect effects.

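### For the dichotomous primary outcomes, a free condition path to the baseline intercept can make the first-slope intervention effect depend on an unstated constraint; that path should be fixed at zero

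*Protocol article*

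**What the plan says.** The protocol article, under Primary analyses of intervention effects, plans on "applying a multilevel latent growth model to follow-up data, accounting for nesting within couples". It then says: "Models will utilize 5 data points (Baseline, 3-, 6-, 9-, and 12-month follow up"). The mean structure has three parts, introduced as follows: "Models will include an intercept (representing the initial outcome value) and two slope factors". On the step at the time of the sessions, the article explains: "The first slope-coefficient will quantify change from baseline to post-intervention". For the later course it adds this on the remaining factor: "The second will capture change over time post intervention". All growth factors are regressed on condition at couple level, and the effect of the intervention is judged from the coefficient and p-value on each of them. The intercept is not excepted.

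The same model is meant for binary data: "Mplus accommodates count and dichotomous outcomes". Drug use is defined through the odds of any use in 30 days, and HIV transmission risk behaviour (TRB) through "three dichotomous behavioral indicators of TRB".

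The section does not say which growth-factor variances and covariances are free, or at which level. The mediation section gives a hint only, namely that "growth factors for the outcome can be regressed on growth factors for the putative mediator at both Level 1 and Level 2".

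**The concern.** Two features combine badly.

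First, couples are randomised after baseline, so any difference between conditions in the intercept is chance. Reading that coefficient as evidence of efficacy is wrong under any variance structure. Leaving the path free also passes the chance difference into the first slope, which is the difference between post-intervention level and intercept.

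Second, only one wave precedes the step. The first slope enters all four follow-ups, so the intercept stands alone at baseline only. A binary outcome carries no variance of its own. One baseline wave therefore gives a proportion and its associations with later waves, and these need not fix the latent scale on which the baseline difference is measured. If that scale is undetermined, the size of the baseline difference subtracted from the post-intervention effect is undetermined too.

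At stake is the p-value for change from baseline to post-intervention, one of the coefficients by which efficacy is judged.

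**Working it through.** There is no figure in the article to reproduce on this point. The stated power comes from a model of one follow-up time-point and does not enter.

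**Inputs from the article.** Five waves; one intercept and two slopes; dichotomous outcomes; 240 couples, so 2 × 240 = 480 men.

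**Assumptions.** Loadings over the five waves: intercept I = 1,1,1,1,1; first slope S1 = 0,1,1,1,1; second slope S2 = 0,0,1,2,3. Probit link. Means 0.8, -0.6 and 0.05. Condition effects -0.4 on S1 and 0.02 on S2. Var(I) = 2.0, var(S1) = 1.5, cov(I,S1) = -0.5. Two groups of 240 men (one factorial main effect), without couple clustering in steps 1 to 3.

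**Step 1: the undetermined scale.** Write P = I + S1 for the post-intervention level, α for means and γ for condition effects. At baseline, Pr(Y = 1) = Φ[(αI + γI·z)/√(1 + var I)]. Multiply αI, γI and the covariances of I with the later factors by k, and 1 + var(I) by k². Every response-pattern probability is unchanged, but

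- mean S1 = αP − k·αI = 0.2 − 0.8k
- γS1 = γP − k·γI
- var(I) = 3k² − 1

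For k = 2: var(I) = 12 − 1 = 11 and mean S1 = 0.2 − 1.6 = -1.40.

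**Step 2: effect on the test, intercept path free.** γP = -0.40. Each cell gives estimate, SE, z for γS1.

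| k | var(I) | mean S1 | no imbalance | γI = +0.15 at k = 1 |
|---|---|---|---|---|
| 0.8 | 0.92 | -0.44 | -0.400, 0.216, -1.85 | -0.520, 0.217, -2.39 |
| 1.0 | 2.00 | -0.60 | -0.400, 0.238, -1.68 | -0.550, 0.240, -2.29 |
| 1.5 | 5.75 | -1.00 | -0.400, 0.311, -1.29 | -0.625, 0.313, -1.99 |
| 2.0 | 11.00 | -1.40 | -0.400, 0.396, -1.01 | -0.700, 0.398, -1.76 |

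No pattern probability in these rows moves by more than 0.00009, which is numerical integration error. An imbalance of 0.15 is ordinary: the SE of γI at k = 1 is 0.205, and 0.15/0.205 = 0.73 standard errors.

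**Step 3: intercept path fixed at zero.** With the path free, Var(γS1) = A − 2kC + k²V, where A = Var(γP), C = Cov(γP, γI) and V = Var(γI), all at k = 1.

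- V = 0.205² = 0.0420
- k = 1: A − 2C = 0.238² − V = 0.0146
- k = 2: A − 4C = 0.396² − 4V = -0.0113
- so C = 0.01295 and A = 0.0405
- check at k = 0.8: 0.0405 − 0.0207 + 0.0269 = 0.0467, SE 0.216, as tabulated

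With γI = 0 imposed, the variance is A − C²/V = 0.0405 − 0.0040 = 0.0365, SE 0.191. No k remains. Without imbalance, z = -0.400/0.191 = -2.09 at every k. With the +0.15 imbalance the estimate is -0.40 − (0.01295/0.0420)(0.15) = -0.446 and z is about -2.3 at every k. A separate probit check (480 men, other assumed values, no clustering) gave SEs of 0.203, 0.255 and 0.321 along the ridge with the path free, and 0.157 throughout with it fixed at zero.

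**Step 4: which structures are affected.** Smallest over largest eigenvalue of the expected information, 240 couples, S2 non-random. A value near zero means not identified.

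| First slope | probit | logit |
|---|---|---|
| not random | 5.4e-3 | 3.9e-3 |
| random at couple level only | 1.7e-3 | 5.9e-4 |
| random at both levels, free covariance with I | 2.6e-17 | 2.1e-7 (SE of mean S1 = 7.0) |

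For 480 men at individual level, zero S1 variance or zero I–S1 covariance gives 1.8e-3 to 7.0e-3 (identified). With all factors random and freely correlated, probit is singular and logit gives 1.2e-7. A continuous score with equal residual variances is identified (rank 7 of 7).

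**The case against.** The strongest objection is that the article never says the first slope has a free person-level variance, let alone a free covariance with the intercept. Condition enters at couple level, and a slope random only there is identified because the two partners replicate the baseline. The mediation section speaks of one slope, not two, so its Level 1 regression does not settle the structure of the primary model. Which variances are free is detail an article commonly leaves to the full plan. All of this stands. A reader might infer that the planned model cannot be identified at all, and the documents do not support that.

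Nor do they show that the constraint would be chosen after the data are seen, since the full analysis plan is not available here.

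Two further points limit the size. Without baseline imbalance the estimated effect does not move; only its standard error does. The range of k is also a choice: between 0.8 and 1.0 the shift in z is small.

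What the objection does not reach is the intercept path. The article does fix that: every growth factor is regressed on condition and each coefficient is read as an effect. The identified alternatives also rest on different assumptions. The couple-level one leans on the baseline association between partners, and for drug use this is distorted by the entry rule. If no couple had two non-users at baseline, with marginal use p, the covariance would be (2p − 1) − p² = −(1 − p)², which is negative, and a shared couple intercept cannot produce that.

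**Conclusion.** The point holds conditionally. Reading the intercept's condition coefficient as an intervention effect is wrong whatever the variance structure. If the first slope is also a person-level random factor freely correlated with the intercept, the binary-outcome first-slope effect equals the post-intervention effect minus k times a chance baseline difference, and the data do not set k (exactly with probit, practically with logit).

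In the illustration the SE ran from 0.216 to 0.396. With a baseline difference of 0.73 standard errors, z ran from -2.39 to -1.76, crossing 1.96 at essentially identical fit. These sizes rest on assumed parameters, a probit link and no couple clustering. They show the direction and possible scale, not a forecast.

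The problem is absent if the first-slope variance, or its covariance with the intercept, is zero, or if the slope is random at couple level only. A reader might also infer that the power claim fails; this point does not bear on it. The change is worth making before unblinding because it is cheap and also gains precision.

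**What to change.** For the dichotomous outcomes:

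1. Set the intercept's condition path to zero, as randomisation after baseline justifies, and do not list the intercept among the factors on which efficacy is judged. All randomised men stay in the five-wave model.
2. State in advance which growth-factor variances and covariances are free at each level, and the constraint that identifies the baseline scale, for example baseline latent variance equal to 3-month latent variance. Constraints that only fix this scale leave the first-slope condition effect unchanged once the path is zero. Setting the first-slope variance to zero is a stronger restriction and should be declared as a modelling assumption.
3. Confirm by a small simulation, with couples and both link functions, that the condition effects are recovered.

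The cost is a few sentences and one simulation. The model would no longer estimate a baseline difference between conditions, which a descriptive baseline table shows anyway. The mean and variance of the first slope would still depend on the stated constraint and should be reported with it.
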